Loss of vision is likewise accompanied by poor balance, postural instability, increased risk of falls and decreased mobility, significantly reducing independence and quality of life in visually impaired (VI) patients. For persons with severe visual impairment, the risk of falls doubles. Adults may also develop “fear of falling” (FOF) and may actually be a more widespread problem that further limits independence, reduces activity level and confidence. Postural sway becomes more pronounced if kinesthetic feedback is perturbed. Similarly, a VI individual may be at greater risk of falling when walking on thick carpet with thick-soled shoes, or on a sandy beach. Therefore, it is important to determine if postural instability or balance deficits exist among the VI population. Static imbalance and compensatory sensory inputs can be reliably determined by measuring postural instability, which is typically done using a computerized force platform. Such platforms are expensive (~$10K-$60K) and rarely available for use by outside researchers. Measuring static balance may be an important surrogate for falls[8](#_ENREF_8). Therefore, we introduce the use of the WBB as an objective measures for static balance which has never been used in the VI population.

Learning to access other non-visual information, such as improving proprioceptive or kinesthetic awareness, is an important factor to consider in severe vision loss. Yoga (e.g. postures, meditation, breathing) has been shown to be a viable intervention to improve sleep disturbances, mood disturbances, and balance, in healthy individuals and those with other chronic diseases. In this pilot study, we aim to evaluate and implement a yoga treatment specifically tailored to the VI population for its feasibility to alleviate sleep disturbances, psychosocial indicators, fear of falling and balance. Measuring participant experience through anonymous exit surveys will further help evaluate the yoga intervention. These data are especially important since there have been no previous publications from other researchers (with the exception of our first paper[9](#_ENREF_9)) involving yoga and interventions in the VI population. Our future research goals include the conduct of clinical trials involving mind-body interventions in visually impaired patients, aiming to decrease secondary symptoms and improve quality of life.

1. **Objectives** (include all primary and secondary objectives)

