***(distinguish research procedures from those that are part of routine care).***

This pilot study will determine the feasibility of the Ashtanga-based Yoga Therapy (YT) in VI subjects participating in a small scale randomized controlled trial. Each session will take approximately 1-3 hours over the course of 12 weeks.

**General Overview:** Baseline measures will be collected prior to the intervention, and participants will be randomized into two groups. An 8-week RCT will be conducted with AYT administered to one group, while the other group is waitlisted; post-tests (all measures from baseline except vision) are collected from all subjects. Then the 8 weeks of AYT are administered to the waitlist group, followed by another set of post-tests. Having a waitlist control group will allow us to compare the effects of AYT on the test measures to that of usual (i.e., no) care, while the final set of post-tests will allow us to compare effect of AYT on the two groups, and determine retention of any gains from the first AYT block.

After explaining the purpose and methods of the study and obtaining informed consent (the consent form will be read to potential participants due to their visual impairment), visual acuity and contrast sensitivity will be evaluated, and background medical and ocular history information will be obtained (30 minutes).

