**AYT *Treatment Validation***

Four measures will be collected to assess the benefits of the AYT, compliance, fidelity of treatment and evaluate the participant’s experience.

1. The *Philadelphia Mindfulness Scale* (PHLMS). This 20-item scale assesses two components of mindfulness, *acceptance* and *awareness*. Total scores on both subscales range from 20 to 100, higher scores reflect greater mindfulness. The PHLMS will be collected at baseline, during week 4 and post- intervention. The PHLMS shows good internal reliability as reported in clinical and non-clinical samples. Total scores on both subscales range from 20 to 100, higher scores reflect greater mindfulness. This scale was chosen because the two components are orthogonal, or independent. Interestingly, *acceptance* is associated with reduced depression, anxiety and rumination but is unrelated to *awareness.* Thus, the PLHMS will allow us to determine distinct benefits associated with *mindfulness* induced by the yoga intervention.

2. *Practice/Homework Logs.* Participants will be asked to complete a weekly log online to report the activity performed, time allotted to the practice and will be used to evaluate compliance.

3. *Treatment Fidelity.* The yoga sessions will be videotaped and a treatment observation log by an independent observer (e.g. research assistant) will be completed during 4-6 yoga sessions chosen randomly to confirm adherence to the yoga treatment.

4. *Exit survey.* Participants will complete a brief, anonymous survey regarding their experience with the AYT. The survey is comprised of open-ended and multiple-choice response items (e.g. treatment expectations).

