-Vestibular problems

-Symptomatic cardiovascular disease

-poorly controlled blood pressure

-history of neurologic disease

-acute orthopaedic problems that affect ambulation

-metastatic cancer

-pregnant women

1. **Drugs/ Substances/ Devices**
2. The rationale for choosing the drug and dose or for choosing the device to be used.

N/A

1. Justification and safety information if FDA approved drugs will be administered for non-FDA approved indications or if doses or routes of administration or participant populations are changed.

N/A

1. Justification and safety information if non-FDA approved drugs without an IND will be administered.

N/A

1. **Study Statistics**
2. Primary outcome variable.

The primary outcome variables are objective and subjective measures of sleep and balance for participants with low vision.

1. Secondary outcome variables.

Secondary measures include FOF, psychosocial mood, AYT validation, physical function and respiratory measures across all subjects.

1. Statistical plan including sample size justification and interim data analysis.

Baseline demographics and clinical variables will be summarized and compared for the 2 groups using descriptive statistics and parametric or non-parametric tests as appropriate. *Primary analysis:* Multiple regression analyses will determine the relationship between vision loss and sleep disturbances. We hypothesize that measures of vision function will be the best predictors of sleep disturbance after accounting for age, general health and psychosocial factors.

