To minimize the discomfort associated with completing study questionnaires and diaries, subjects will be informed that they are free to refrain from answering any questions that make them uncomfortable of that they perceive as being personal or sensitive and do not wish to share as part of the study. If information gathered through the research indicates that a participant needs urgent psychiatric care (e.g. expressed suicidality), Drs. [name] and [name] will be immediately notified and the subject will be referred for immediate care.

Prior to the intervention, participants will notify the instructor of all pre-existing physical injuries.

The instructor will note each condition for each subject and suggest modifications for each pose based on subjects’ responses. To reduce the risk of injury, subjects will be advised to never force or strain themselves during exercise. If subjects feel pain, they will be advised to stop immediately and seek medical attention if necessary.

Testing of physical abilities through Balance and Physical function tests pose a very small possibility of falls or injury. However, subjects who feel uncomfortable can opt out of the balance tests. Research coordinators administering the tests are trained to identify individuals who may be at risk of injury during testing and will not perform tests on subjects for whom they feel testing would be unsafe. Coordinators will be trained in methods to prevent injury in cases where a subject loses his/her balance or begins to fall. No injuries have occurred in over 200 individuals tested with this protocol in other studies at the Wilmer Eye Institute and in over 10,000 subjects studied in other protocols[19](#_ENREF_19).

Another risk that requires management is the potential breach of patient confidentiality. The study investigators have been trained in the methods necessary to protect subjects’ privacy and every attempt will be made to maintain records and data in secure databases and areas. This study poses minimal additional risk. The societal benefits outweigh these risks.

1. Steps taken to minimize the risks.

If dilating drops are used, study personnel are trained in detecting ophthalmic adverse effects, including acute glaucoma.

1. Plan for reporting unanticipated problems or study deviations.

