In the very unlikely event that a serious adverse event occurs, the study co-investigator(s) will immediately notify the IRB within 24 hours of the occurrence, using the standard JHU Adverse Event report form.

1. Legal risks such as the risks that would be associated with breach of confidentiality.

N/A

1. Financial risks to the participants.

N/A

1. **Benefits**
2. Description of the probable benefits for the participant and for society.

There will be no direct benefit to the subjects as a result of performing the vision tests, questionnaires, or balance tests. We will share the results of the vision tests with the subjects. At the end of the study, subjects’ visual status will be monitored for any significant changes by a licensed clinician, which may be considered a benefit. Any new information regarding the subjects’ vision may be shared with their eye care provider, at the subjects’ request.

Potential benefits may occur during the yoga intervention; however, this has not been previously demonstrated with scientific study among this patient population. Other types of patient populations have experienced decreased stress, anxiety, fatigue, depression, improved balance, and sleep as a result of yoga interventions. The anonymous exit surveys may allow the subjects to learn more about the experiences of other visually impaired subjects as a result of their AYT practice.

1. **Payment and Remuneration**
2. Detail compensation for participants including possible total compensation, proposed bonus, and any proposed reductions or penalties for not completing the protocol.

Participants will receive a free yoga mat and AYT instruction, as well as parking validation if they travel to our center with a sighted companion.

1. **Costs**
2. Detail costs of study procedure(s) or drug (s) or substance(s) to participants and identify who will pay for them.

The subjects will not be responsible for any costs directly related to the project, with the exception of transportation-related costs to our center.

Funding is provided by a scholarship from the Delta Omega public health honor society and by the [name] Wilmer Research Grant.

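### Only serious adverse events have a reporting rule; falls and non-serious yoga injuries are not systematically collected in either arm

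*Protocol*

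**What the plan says.** The protocol's Abstract motivates the balance work partly through falls: "For persons with severe visual impairment, the risk of falls doubles". Study Procedures gives the purpose: "This pilot study will determine the feasibility of the Ashtanga-based Yoga Therapy (YT) in VI subjects participating in a small scale randomized controlled trial".

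Under Study Statistics, the outcomes are set out as follows: "The primary outcome variables are objective and subjective measures of sleep and balance for participants with low vision"; "Secondary measures include FOF, psychosocial mood, AYT validation, physical function and respiratory measures across all subjects". Fear of falling is on the list. Falls, injuries and adverse events are not.

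In the Risks section, the item on reporting unanticipated problems and deviations is answered by one sentence. It opens "In the very unlikely event that a serious adverse event occurs" and has the co-investigators tell the IRB within 24 hours, on the university's standard form. For discomfort during yoga, the same section says: "If subjects feel pain, they will be advised to stop immediately and seek medical attention if necessary". No recording step follows.

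The practice log is described under AYT Treatment Validation: "Participants will be asked to complete a weekly log online to report the activity performed", together with the time spent, as a measure of compliance. Study Statistics adds that the logs will show progress in difficulty.

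The Intervention Phase section sets one instructor-led class a week and at least two home sessions a week, guided by an audio CD, for 8 weeks. Allocation is to two equal groups, with a stated minimum of 10 subjects. Study Statistics says the pilot will help develop the intervention and plan larger trials.

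**The concern.** The protocol measures a possible surrogate for falls (static balance) and the fear of falls, but not the falls themselves. It studies a physical intervention in people whose fall risk it describes as doubled, with most planned sessions away from the instructor. It nevertheless provides no systematic way to learn whether anyone fell, strained something or stopped because of pain.

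Three things are at stake:

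- A judgement that the programme is feasible and ready for a larger trial could rest on events not having been asked about rather than on their absence.
- The removal criteria allow withdrawal for repeatedly missed appointments, and no reason for stopping is collected. A participant who stops because of pain could be classed as non-compliant, which would distort the feasibility result itself.
- The first 8 weeks are the only period with a concurrent untreated group. Afterwards the waitlist group receives yoga too.

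This is a matter of data collection, which belongs in the protocol. An analysis plan cannot tabulate answers that were never requested.

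**Working it through.** The plan gives no figure on this point to reproduce. It states that a sample size calculation does not apply, and it gives no absolute fall rate.

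**Step 1. Search for a capture step.**

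| Source in the protocol | What it yields | Falls or non-serious injury, both arms? |
|---|---|---|
| Serious-event notice (Risks) | Serious events to the IRB, either arm | Only if serious |
| Advice on pain (Risks) | Instruction to the participant | Not recorded |
| Fear-of-falling question and scale (Balance and FOF) | Worry about falling | No |
| Practice log (AYT Treatment Validation; Study Statistics) | Activity, time, progress in difficulty | Not mentioned |
| Class video (Background; AYT Treatment Validation) | 4-6 classes scored for adherence to the yoga protocol | Incidental, classes only |
| Exit survey (AYT Treatment Validation) | Anonymous views on the yoga | Incidental, not linkable |
| Journals (Intervention Phase) | Encouraged free text | Incidental |

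Other provisions cover a change in vision, urgent psychiatric need and the effects of dilating drops. None concerns falls or yoga injuries. The statement in Risks that no injuries occurred in over 200 and over 10,000 people refers to balance and physical testing, not to yoga.

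**Step 2. Share of sessions at home.** One class plus two home sessions a week for 8 weeks: 2 × 8 = 16 of 3 × 8 = 24, or two thirds. This uses the 8-week course. The section on study duration speaks of a 12-week intervention phase with 12 visits, so the count depends on that reading.

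**Step 3. What full collection could show at the minimum size.** With zero events in n subjects, the exact one-sided 95% upper bound is 1 − 0.05^(1/n).

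- All subjects, n = 10: 1 − 0.05^(1/10) = 25.9%.
- One arm, n = 10/2 = 5: 1 − 0.05^(1/5) = 45.1%.

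**Step 4. What the serious-event rule alone might miss.** The rates here are assumptions. Take an 8-week fall risk p of 10%, 20% or 30% (5%, 10% or 15%, doubled), and suppose a share s of 5% to 20% of falls is serious. The chance of at least one faller among 10 is 1 − (1 − p)^10. The chance that the rule registers at least one is 1 − (1 − p·s)^10.

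| p | At least one faller | At least one serious, s = 5% | At least one serious, s = 20% |
|---|---|---|---|
| 10% | 65% | 5% | 18% |
| 20% | 89% | 10% | 34% |
| 30% | 97% | 14% | 46% |

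Across these assumptions a fall in the study is likely (65-97%), while the existing rule would register one with a chance of about 5-46%.

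**The case against.** The other side has several fair points.

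- A reader might infer that the trial will end with no data on falls or injuries. The protocol does not support that. A serious fall or injury in either arm would be reported, and the survey, video and journals could show some yoga injuries. What stands is that these sources are incidental and that, apart from the serious-event rule, they say nothing about the waitlist control period.
- A reader might infer that home practice goes unmonitored. That is also too strong. The instructor sees participants weekly, notes pre-existing injuries and suggests modifications to poses. Systematic recording is what is missing.
- The serious-event sentence says what goes to the IRB; it does not say that other events will go unrecorded. No log form is shown, so its full content is unknown. This is true, but no passage provides for collecting such events, so following the text as written would not produce the data.
- Falls are neither an objective nor an outcome, sleep is at least as prominent in the rationale, and the protocol promises no safety conclusion. This limits the weight of the point. It does not remove it, because the pilot is meant to inform the intervention's further development.
- With about 5 subjects per arm, no useful comparison of event rates is possible. This stands in full.

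**Conclusion.** The point holds in a limited form. Serious adverse events have a reporting rule. Falls and non-serious yoga injuries have no systematic collection in either arm, and an analysis plan cannot repair that later. The planned analyses of sleep and balance are unaffected, and no figure in the protocol is wrong. The loss is to the feasibility assessment: comparable counts of falls and injuries, and the ability to tell stopping for pain from non-compliance.

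The conclusion rests on reading the listed measures as complete for this purpose. The probabilities for falls rest on assumed rates and only illustrate the likely size of the loss. Even with full collection the data would be descriptive, given the bounds at the stated minimum size. It is a cheap and worthwhile improvement, not a defect that undermines the trial.

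**What to change.** Add two items to the weekly online form:

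1. The number of falls this week.
2. Any pain or injury (yes/no) and, if yes, whether it was related to yoga and whether it led to stopping practice.

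Ask both items in identical form of both arms during the first 8 weeks, and of the waitlist arm again during its yoga block. Tabulate the counts by arm, descriptively, as part of the feasibility results, with no between-arm test.

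The cost is small, and no visits are added. It is not nil, however. The Intervention Phase section places the weekly questionnaires during the intervention, and although the Psychosocial Questionnaires section makes the stress scale weekly, it does not name the arms. Weekly contact with waitlist participants is therefore not established, and they may need a short new weekly online form, possibly with some follow-up of non-responders.
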